## Abstract

**Background:**

Primary care is the principle setting for depression treatment; yet many older African Americans in the United States fail to report depressive symptoms or receive the recommended standard of care. Older African Americans are at high risk for depression due to elevated rates of chronic illness, disability and socioeconomic distress. There is an urgent need to develop and test new depression treatments that resonate with minority populations that are hard-to-reach and underserved and to evaluate their cost and cost-effectiveness.

**Methods/Design:**

Beat the Blues (BTB) is a single-blind parallel randomized trial to assess efficacy of a non-pharmacological intervention to reduce depressive symptoms and improve quality of life in 208 African Americans 55+ years old. It involves a collaboration with a senior center whose care management staff screen for depressive symptoms (telephone or in-person) using the Patient Health Questionnaire (PHQ-9). Individuals screened positive (PHQ-9 ≥ 5) on two separate occasions over 2 weeks are referred to local mental health resources and BTB. Interested and eligible participants who consent receive a baseline home interview and then are randomly assigned to receive BTB immediately or 4 months later (wait-list control). All participants are interviewed at 4 (main study endpoint) and 8 months at home by assessors masked to study assignment. Licensed senior center social workers trained in BTB meet with participants at home for up to 10 sessions over 4 months to assess care needs, make referrals/linkages, provide depression education, instruct in stress reduction techniques, and use behavioral activation to identify goals and steps to achieve them. Key outcomes include reduced depressive symptoms (primary), reduced anxiety and functional disability, improved quality of life, and enhanced depression knowledge and behavioral activation (secondary). Fidelity is enhanced through procedure manuals and staff training and monitored by face-to-face supervision and review of taped sessions. Cost and cost effectiveness is being evaluated.

**Discussion:**

BTB is designed to bridge gaps in mental health service access and treatments for older African Americans. Treatment components are tailored to specific care needs, depression knowledge, preference for stress reduction techniques, and personal activity goals. Total costs are $584.64/4 months; or $146.16 per participant/per month.

**Trial Registration:**

ClinicalTrials.gov #NCT00511680

## Background

Depression, a common, debilitating but treatable condition among older adults, contributes to poor quality of life and functional decline and is one of the most serious complications of chronic conditions [1]. Depression worsens health conditions and exacerbates disability contributing to a pernicious downward spiral [2]. Even mild to moderate depressive symptoms are associated with difficulties performing daily activities and may amplify and prolong inflammatory responses after infection [3].

Depression prevalence ranges from 15 to 17%, but rates are twice as high among individuals with physical health problems, functional disabilities, low socioeconomic status and receiving home care or related services [4]. Older African Americans in the United States (USA) are at particular risk due to high rates of chronic illnesses associated with depression (diabetes, heart disease), and social, economic and environmental detriments. Evidence also suggests higher prevalence of depressive symptoms for this group than previously reported [5]. The African American Health Study of 998 community-dwelling African Americans found 21.1% with clinically relevant depressive symptomatology [6]. Of 150 older poor African Americans attending outpatient rehabilitation, 30% scored positively for depression [7]. A survey of 156 African American senior center members found 24.2% with mild to moderate severe depressive symptoms [8].

In the USA, most older adults are screened for depression and treated in primary care settings, yet frequently do not receive the recommended standard for depression care. A consistent finding is that older African Americans tend to be underdiagnosed in primary care and underutilize mental health services [9,10,11)]. Moreover, with few exceptions, mental health treatments have not been developed or evaluated specifically for older African Americans [12]. However, when depression treatments including medication and/or cognitive therapies are provided, outcomes for this group are beneficial and long-lasting [13].

Previously tested system-level depression studies target primary care settings. These interventions principally involve collaborative care management treatments with large trials reporting impressive treatment effects [14-17]. However, these models have not been developed specifically to outreach to older African American communities and, with few exceptions outcomes have not been evaluated for this group [12]. Also, these models are difficult to sustain due to limitations in clinical and reimbursement structures unsupportive of care coordination activities essential to their success.

Moreover, studies consistently show that African Americans continue to obtain poorer quality of depression care than White patients [9,10,18,19]. Barriers to depression care persist at the patient level and include stigma and lack of depression knowledge [11,20]; provider level due to lack of knowledge and training in assessment and treatments [9], and systems level due to lack of care coordination and sustainable infrastructures [21]. Persistence of mental health disparities for older African Americans in the USA, higher depression rates than previously found, coupled with continued unequal access to culturally relevant mental health treatments, point to the need to advance more powerful care models and interventions for this group. Developing and testing new service approaches that improve access to depression detection, referral and treatment tailored to treatment preferences of older African Americans remains an important public health priority [22].

An overlooked and underutilized system of care for depression detection and treatment is the aging network of services, a federally and state-funded system in the USA providing an array of social services to over 9 million older adults, many of whom are vulnerable and underserved [23,24]. One promising depression program building upon previously tested approaches and offered through the aging network, Healthy IDEAS (HIDEAS; Identifying Depression, Empowering Activities for Seniors), has shown modest positive client outcomes including enhanced depression knowledge, decline in symptomatology, and clinician adoption [25,26]. HIDEAS involves systematic screening, depression education, referral and linkage and engaging clients in behavioral activation by case managers. Nevertheless, HIDEAS was not tested in a randomized trial and less than half (44.7%) of the 94 participants received behavioral activation, with only a small percentage being African American [26].

A few studies evaluating intervention delivery at home suggest that older adults prefer home over clinic-based treatment [8], and home sessions may lead to better treatment acceptance [16], fewer nursing home admissions and in-patient care days, as well as be cost effective [27].

We designed Beat the Blues (BTB) to be delivered through a community-based organization such as senior centers. Senior centers routinely assess older adults for service needs and health status, serve as initial contact for a continuum of aging services, and provide a safety net offering meals, health checks, care management and referral services. Individuals reluctant to consult primary care physicians or mental health specialists may be more comfortable disclosing depressive symptoms to skilled senior center staff with whom they have rapport. Although senior centers potentially reach large numbers of vulnerable older adults at risk for behavioral health problems, most do not systematically screen for depressive symptoms or offer evidence-based depression treatments. Building senior center capacity to detect depressive symptoms and deliver effective non-pharmacological treatments may compliment other care systems and optimize mental health programming for underserved.

BTB builds upon the successes and lessons learned from prior depression treatment efforts but it also differs from previous efforts in important ways. First, delivery is integrated with staffing and daily routines of a community-based agency, a senior center versus a mental health clinic or primary care setting, enhancing potential for normalization and sustainability in that setting. Second, BTB is culturally sensitive; its name reflects the characterization of depression by the target group; and treatment components resonate with their preferred coping approaches. As activity is a primary strategy for coping with adversity among older African Americans [28], behavioral activation was chosen as an essential component of BTB. This approach, shown to be effective in previous depression trials, helps participants reengage in self-identified meaningful activities. Third, while each treatment component of BTB has been shown to be effective in other trials, they have not been combined into one program and systematically tested with older African Americans.

BTB is currently being formally evaluated in a prospective parallel two-group randomized trial. The study is designed as a practical trial embedded in a senior center. This article describes trial procedures, the intervention, enrollment, and program costs. Trial results and cost effectiveness will be reported in future articles.

## Methods/Design

The BTB study protocol received ethical approval from the Institutional Review Board at Thomas Jefferson University (Control #06F.551) in which the protocol was initiated; with ethical approval also subsequently received by the Institutional Review Board at Johns Hopkins University (Control # NA-00046775) upon appointment of the Principal Investigator and lead author. Also, a Federal Wide Assurance Agreement between the senior center agency (Center in the Park) in which the study was implemented and Thomas Jefferson University was obtained.

BTB reflects a partnership between a university research center and a senior center with each contributing to the plan and execution of the study and model design while preserving internal validity and control of a randomized trial. Agency staff are trained in human subjects and participate in recruitment efforts, conduct depression screenings, and deliver the home intervention; research staff provide oversight of trial procedures, jointly participate in recruitment efforts, train agency staff in depression screening, implement randomization procedures, and provide oversight of intervention delivery and monitoring of treatment fidelity. The design optimizes experimental control while building capacity of the participating senior center to screen and deliver BTB; hence, maximizing potential for sustainability and self-sufficiency at trial conclusion if BTB is efficacious and cost-effective. Additionally, the partnership enables the senior center to access mental health researchers and experts to provide oversight and guide implementation. The academic institution maximizes recruitment and trial success through involvement upfront of end users of the intervention. This approach may also enhance sustainability if the intervention is shown to be effective.

General procedures include two sequential depression screenings of individuals by senior center staff over two weeks using the Patient Health Questionnaire (PHQ-9). Those eligible (PHQ-9 ≥ 5) and willing provide written consent using an approved Institutional Review Board (IRB) form (Thomas Jefferson University IRB control #06f.551) and receive a baseline home interview conducted by academic partners. Participants are then randomized to receive BTB immediately or 4 months later (wait-list control). All participants are reassessed at 4 and 8 months by academic partners who remain masked to study assignment. The design allows for a true two-group comparison at 4 months to evaluate intervention effects on symptom severity (primary end point), quality of life indicators, anxiety, depression knowledge, and functional disability (secondary endpoints); an evaluation of long-term (8 months) effects for the initial treatment group; and whether wait-list controls derive similar benefits from 4 to 8 months. Treatment fidelity is enhanced through use of treatment manuals, session implementation checklists, audiotaping and rating of randomly selected sessions, one-on-one supervision and bi-weekly group debriefing sessions involving structured case presentations and review of treatment documentation.

### Aims and study hypotheses

Our primary aim is to test the immediate effect of the intervention at 4-months on symptom severity (PHQ-9 severity score) in African American older adults (primary trial outcome; between group comparison). Our hypothesis is that participants in the initial treatment group will report fewer depressive symptoms in comparison to control group participants receiving usual care. We also seek to test the maintenance effect of the intervention at 8-months on depression (within group comparison). Our hypothesis is that participants in the initial treatment group will maintain reduced symptom presentation from 4 to 8 months and the wait-list control group will show similar reductions in depressive symptoms as the initial treatment group (within group comparison).

A secondary aim is to evaluate whether BTB has immediate (4 months) and long-term (8 months) effects on quality of life indicators, functional difficulty, anxiety, and depression education and behavioral activation levels. We expect that the initial treatment group will show improvements in these areas relative to the wait-list control group, that improvements will be maintained at 8 months and that the wait-list control group will demonstrate similar improvements at 8 months following their receipt of the intervention.

Several exploratory aims are also proposed. We will evaluate the mechanism of action, or pathways, by which treatment gains are obtained. Given that behavioral activation represents conceptually the key active ingredient of the proposed intervention, we plan to evaluate its mediational effect. We will also evaluate whether the intervention has a differential treatment effect based on a study participant's gender, age, and living arrangement (alone or with others). Given that previous research suggests that participant characteristics may moderate depressive symptoms and treatment outcomes, these exploratory analyses will provide insight as to whether this particular treatment benefits some groups more than others.

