### Measures

In selecting measures for this study, we chose those with known reliability and validity; sensitivity to change that is expected to occur as a consequence of intervention; relevance to and wide usage in depression research, and acceptability by the target population. Our primary outcome measure is the Patient Health Questionnaire (PHQ-9), a brief, 9-item self-report measure specifically developed as an assessment tool for the diagnosis of depression in primary care. In addition to its psychometric soundness and demonstrated reliability, validity, sensitivity and specificity, the measure is also widely used in community-based settings and research trials. It yields a depression severity score (0 to 27) and a diagnostic category (minimal to none, mild, moderate, moderate severe, severe) mapping on to the 9 DSM-IV. Administration involves initially asking two items (loss of interest; feeling upset, distressed or depressed). Individuals reporting that either symptom occurs more than half the time over past two weeks are administered 7 other items [29]. Thus, two scores can be derived: symptom severity and categorical diagnosis. We also consider as a complementary secondary outcome a change in categorical diagnoses in which we seek to determine the number of persons who shift to none to minimal diagnostic category at 4 months. A categorical approach provides a clinical interpretation of treatment efficacy and also whether the intervention addresses certain syndromes better than others (e.g., minor depressive disorder may be more responsive to the proposed intervention than major severe depression). While the PHQ-9 is a self-report measure, self-report has been shown to be highly associated with clinical determinations. Also, the measure has been shown to be effective when administered in person or via telephone. The secondary outcome measures for the trial are presented in Table 1.

**Table 1 T1:** Secondary Outcome Measures for BTB Trial

Domain	Description of Measure	# of Items
Functional difficulties	Level of difficulty (1 no difficulty to 5 unable to do due to health problem) with items reflecting ambulation, self-care and instrumental activities of daily living [31].	18
Depression knowledge	Self-efficacy concerning ability to recognize and treat depression rated from absolutely confident (4) to not confident at all (1) [32].	10

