### BTB Intervention

Up to 10 one hour sessions occur over 4 months. A home visit can be replaced with check-in telephone calls once steady progress is demonstrated. Sessions integrate five treatment components previously shown to be effective and modified in BTB to resonate with cultural preferences: case management, referral and linkage, depression education, stress reduction techniques, and behavioral activation. (Table 2) Critical is tailoring to participants' depression knowledge level, care management needs, and self-identified goals and behavioral activation plans.

**Table 2 T2:** Intervention Component, Content, and Modification for Target Population

Component	Content	Modifications for Target Population
Education [14,25]	Education provides foundation for introducing other elements of the intervention. It enhances readiness of individuals to address emotion-laden concerns. Specifically, education was provided on: 1) depressive symptoms, 2) how to talk to doctor about symptoms; and 3) relationship of depression to activity and negative cycle of disengagement	1) Used participant's words and own labeling to describe feelings (e.g., "I am feeling blue"). 2) With rapport and only over time, feelings are then labeled as symptoms of "depression." 3) Discussed how to talk to a doctor of a different race. 4) Withdrawal of activity related to specific activities person identified as valued. 5) Used visual mood rating scales and calendars with big print to minimize vision and literacy challenges.
Care management [12,14]	Care management has been found to be more effective than therapy or medication alone for low income elders for whom financial, functional disability and lack of social resources may contribute to depressive symptoms. Specifically this involved: 1) assessment 2) coordination with other services/care management; 3) problem identification and resolution	1) Considered a wide range of care needs most relevant to this population including home repairs, financial concerns, home and neighborhood safety, family conflict. 2) Housing and neighborhood difficulties were evaluated to determine whether person could remain in setting.

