Referral and linkage [14,25]	Referrals and linkages are derived from the care management assessment and may include: 1) physician referral for medication review and management; 2) link to psychiatric/psychological follow-up; 3) link to physician for chronic disease management; 4) referral and linkage to other services (e.g., home repairs, financial or legal advisors)	1) Referrals made to vetted community-based service providers sensitive to participants' resources and cultural preferences. 2) For individuals identified as in need of more mental health support, helped make bridge to these services
Stress reduction	Provides immediate, easy-to-learn technique to reduce stress of person and introduce relationship of action and mood change. Specific techniques included: 1) deep breathing; 2) counting; 3) use of music of personal interest	1) Recognition of importance of spirituality and possible objection to meditation as a stress reduction activity. 2) Use of relaxation CD/Tape with participants who did not want to participate in deep breathing exercise.
Behavioral Activation [14,16,25]	Approach is designed to increase frequency of pleasant events and provide positive reinforcement. Self-identification of goals/action plan promotes activation. The approach involves: 1) identification of valued activities and goals; 2) establishment of plan of action for goal attainment; 3) monitoring and adjustment of plan/goals; and 4) identification of new goals and steps to attain them and reinforcement and validation.	1) Awareness and identification of appropriate community-based programs and services that could help participants link to meaningful activities. 2) Use of "Pro/Con" lists and motivational interviewing in formulation of feasible goals. 3) Link individual to senior center to enable continuation of activity participation in a planful, structured setting.

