Initial sessions occur weekly and then bi-weekly. In session one, building rapport and a therapeutic relationship begins; also, interventionists assess care management needs and begin education about depressive symptoms making connections between behavior and mood. Explained is that with depression, activities once pleasurable are often stopped which may heighten symptomatology. Likewise, previously pleasurable activities may no longer be pleasurable. Interventionists also discuss sharing depressive symptoms with physicians (if medication may be necessary or for future consideration) and strategies to use when physicians are of a different race. Interventionists introduce deep breathing as a basic stress reduction technique and help participants identify stressful points in the day for its use. In sessions 2-3, interventionists engage participants in simple problem solving to resolve identified care management needs (medical, housing repairs, relocation needs, social, benefits/entitlements), and works on a care management plan involving coordination, referral and linkages to other services if necessary. Other stress reduction techniques (counting, music) are introduced to provide additional tools. In sessions 4-5, interventionists continue addressing care management needs and introduce behavioral activation. Interventionists review daily routines and help participants select a goal and specific activity to add pleasure and personal satisfaction. Active problem solving and motivational interviewing techniques help participants achieve identified activity goals. Potential barriers in carrying out activities are identified and solutions derived which may also require care management (arranging transportation) to engage in desired activities. Sessions 6-8 involve reinforcement of activity engagement, identification of new activity goals and specific steps to achieve them. In sessions 9-10, interventionists review and reinforce all techniques, help participants identify and use behavioral activation strategies, and obtain closure. Approximately 6-7 sessions are devoted to behavioral activation.

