For exploratory aims, we seek to evaluate the mediational role of behavioral activation. We will use separate regressions in which the first regression will evaluate the relationship between 4 month values of the behavioral activation scale (the mediator) and symptom severity as measured by the PHQ-9 at 4 months. The second regression will evaluate the relationship between group assignment (the independent predictor variable) and symptom severity at 4-months (PHQ-9, the criterion). The third regression will evaluate the relationship of treatment assignment (predictor) to PHQ-9 severity scores (criterion) after entering behavioral activation values (mediator). To evaluate the strength of the mediation effects, we will compute the ratio of the unstandardized betas for treatment assignment (beta from regression III divided by beta from regression II) with values less than 1.00 indicating potential mediation. We will repeat these analyses using 8-month values of the PHQ-9. Another exploratory aim is to evaluate whether the intervention has a differential treatment effect based on a study participant's gender, age, or living arrangement (alone/with others), factors which have been shown to be differentially related to depression. To evaluate differential treatment effects at 4-months, we will use a similar analytic strategy as for the main effect model. ANCOVAs will be used in which the covariates will be the baseline value and specific participant characteristic (e.g., male/female; live with other or alone; age 60-64 versus 75+). We will then add an interaction term of group assignment by participant characteristic.

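### The exploratory mediation analysis enters behavioral activation alone in a five-component intervention, so it may credit activation with the effect of correlated pathways, and reading any ratio below 1.00 as potential mediation cannot show this

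*Protocol article*

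**What the plan says.** Under Aims and study hypotheses, the protocol article lists mechanism of action among its exploratory aims and gives its reason for choosing one mediator: "Given that behavioral activation represents conceptually the key active ingredient of the proposed intervention, we plan to evaluate its mediational effect". The Analytic plan repeats the choice ("For exploratory aims, we seek to evaluate the mediational role of behavioral activation") and writes the models out. Regression I relates 4-month activation to 4-month PHQ-9. Regression II relates assignment to 4-month PHQ-9. For the last: "The third regression will evaluate the relationship of treatment assignment (predictor) to PHQ-9 severity scores (criterion) after entering behavioral activation values (mediator". The index is the treatment beta from regression III divided by that from regression II, and a value under 1.00 is taken to indicate potential mediation.

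The BTB Intervention section describes a package: "case management, referral and linkage, depression education, stress reduction techniques, and behavioral activation". The components share sessions: "In sessions 4-5, interventionists continue addressing care management needs and introduce behavioral activation". Activation has the largest share of up to 10 sessions: "Approximately 6-7 sessions are devoted to behavioral activation". Table 2 lists other routes to benefit, such as "physician referral for medication review and management" under referral and linkage.

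One of the other processes has its own scale. Table 1 defines depression knowledge as "Self-efficacy concerning ability to recognize and treat depression rated from absolutely confident (4) to not confident at all (1". The secondary aim expects BTB to improve both depression education and activation. Table 1 has no scale for care management or referral.

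**The concern.** The stated aim is to learn by which pathways gains are obtained, but only one pathway enters the model. The others also begin after randomisation and differ by arm, so randomisation does not separate them from activation. Participants who attend more sessions receive more of every component, and some content overlaps, so a within-arm correlation between activation and another process is plausible.

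If that correlation exists, an activation coefficient estimated alone partly stands in for the other process. An interval or baseline adjustment would not remove this, because the competing path is itself caused by assignment. The article says the exploratory analyses are meant to inform refinement and wider use of the programme, so a misattributed mechanism could mislead the choice of what to emphasise.

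**Working it through.** The plan gives no figure for this analysis, so there is none to reproduce. The check asks when the planned ratio misattributes an effect, and by how much.

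**Set-up.** T is assignment. M1 is the activation score, M2 is another component's process, and both have unit residual SD. M1 = a1·T + e1 and M2 = a2·T + e2, with within-arm correlation r between e1 and e2. Activation is made inert: PHQ-9 = b2·M2 + error.

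- Regression II: the treatment beta is a2·b2.
- Regression III: given T, M1 predicts M2 with slope r. The activation beta is therefore r·b2, and the treatment beta is b2·(a2 − r·a1).
- Ratio III/II = 1 − r·a1/a2.

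False credit therefore needs both a1 ≠ 0 (BTB moves activation) and r ≠ 0. If either is zero the ratio is 1.00 and the other path's effect stays in the treatment coefficient.

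**Size.** The documents give no values for a1, a2, b2 or r; all are assumed.

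| r | a1 = a2 = 0.5 SD: ratio | a1 = 0.3, a2 = 0.5 SD: ratio |
|---|---|---|
| 0.2 | 0.80 | 0.88 |
| 0.3 | 0.70 | 0.82 |
| 0.4 | 0.60 | 0.76 |
| 0.5 | 0.50 | 0.70 |

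So 20–50% of the effect goes to an inert mediator in the second column, and 12–30% in the third.

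**The planned ratio, simulated** (4,000 trials, N = 172 as in the sample-size paragraph, a1 = a2 = 0.8, b2 = −0.5):

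| Scenario | Median ratio | Ratio below 1.00 |
|---|---|---|
| r = 0 | 1.00 | 51% |
| r = 0.2 | 0.81 | 87% |
| r = 0.3 | 0.71 | 95% |
| r = 0.5 | 0.51 | 99% |
| r = 0.5, BTB does not move activation | 1.00 | 49% |

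With no mediation, sampling error alone puts the ratio below 1.00 in about half of trials. When both paths are real and equal (b1 = b2 = −0.35, true ratio 0.50), the median is 0.51 at r = 0 and 0.35 at r = 0.3, so a genuine activation effect is overstated.

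**Would a proper test of the indirect path be enough?** With n = 186 (close to 208 × 0.9 = 187.2), inert activation, 0.5 SD shifts, b2 = −0.4, baseline adjustment and a joint-significance test, the one-mediator model declares mediation in 17%, 34%, 56% and 74% of trials at r = 0.2, 0.3, 0.4 and 0.5. With the other path entered as well, the rate is about 5%. The joint test is not in the plan, so these are not error rates of the planned procedure. They show that adding a test does not by itself cure the problem.

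**Limits of adding the knowledge score.**

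- If an unmeasured component does the work, and knowledge correlates 0.2 with it and with activation (assumed; no baseline terms), adding knowledge lowers false mediation only from 17/34/53/73% to 13/28/46/68%.
- If activation itself raises knowledge, adding knowledge removes part of activation's true effect. For example, suppose BTB raises activation by 0.5 SD and half of activation's −0.4 effect passes through knowledge. The indirect effect then falls from 0.5 × (−0.4) = −0.20 to 0.5 × (−0.2) = −0.10.

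**The case against.** The strongest reply is that regression III keeps assignment in the model, so benefit that bypasses the activation score is not moved to activation. This is correct. A reader might infer that whatever education, care management or medication referral achieves is automatically booked to activation. The documents do not support that: it happens only under the two conditions derived above.

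Second, the mediator is the participant's activation score, not the activation sessions. Table 2 ties education and stress reduction to the link between activity and mood, and care management may arrange transport to activities. Benefit that these components produce by raising activation is properly counted through activation. This also stands.

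Third, the aim is exploratory, no power was calculated for it, and the reading is only potential mediation. A reader might infer that the trial would announce activation as the proven active ingredient. The article does not say so; it offers that label as a conceptual premise, and testing one theory-based mediator is a legitimate choice of scope. This lowers the severity but leaves the interpretive gap.

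Fourth, further mediators might appear in a fuller document. That is possible, but the article writes out all three regressions and the reading rule, and it is those that are assessed here.

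Fifth, a two-mediator model has faults of its own, as the last step of the working shows. For that reason it should stand beside the planned model and not replace it.

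**Conclusion.** The point holds in a limited form. The planned analysis cannot separate activation from a correlated pathway, and a ratio below 1.00 with nothing further is weak evidence of any mediation. If BTB raises activation and activation is correlated within arms with another component's path, part of that path's effect may be credited to activation: 20–50% for correlations of 0.2 to 0.5 with equal shifts, and 12–30% if activation moves by only 0.3 SD against 0.5 SD for the other path. These figures rest wholly on assumed inputs, including an inert activation score and a single other path carrying the whole effect, so they illustrate the problem and do not forecast the result. The roughly 50% rate of ratios below 1.00 under no mediation needs neither a correlation nor a competing pathway that misleads; it is sampling error around 1.00.

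The primary comparison is untouched. Severity is minor.

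**What to change.** In the exploratory mediation paragraph of the Analytic plan:

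- Keep the one-mediator model, but report the activation indirect effect with a bootstrap interval instead of relying on a ratio below 1.00.
- Report beside it a model that also enters the 4-month depression knowledge/self-efficacy score, with baseline values.
- Describe activation as a distinct mediator only if its indirect effect is supported in both models. Otherwise describe the result as a path shared with other BTB components.
- State as limitations that care management and referral have no measure and cannot be adjusted for, and that the second model may under-credit activation if activation itself raises knowledge.

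The cost is a few sentences and a few lines of code, because activation and knowledge are both already secondary outcomes. The interval for activation will be somewhat wider in the second model. Neither model settles direction, since activation and PHQ-9 are both taken at 4 months.
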